#### Participant timeline

A flowchart of the study and a timeline is presented in Fig. 2.

**Fig. 2 Fig2:**
[figure not shown]
Study flowchart

### Study outcomes

#### Primary outcomes

The primary outcome of this study is the complete response rate, defined as a pCR or a sustained cCR. A pCR is defined as the absence of residual tumour cells in the complete resected specimen including all resected regional lymph nodes (ypT0N0) according to the 8th edition of the UICC TNM classification of malignant tumours [36]. A sustained cCR is defined as the absence of viable tumour tissue based on MRI and endoscopic evaluation at 1 year after the last day of chemoradiotherapy.

#### Secondary outcomes

Secondary outcomes are regrowth rate, local recurrence rate, distant metastases rate, 3- and 5-years regrowth free survival (RFS), 3- and 5-years local recurrence free survival (LRFS), 3- and 5-years distant metastases free survival (DMFS), 3- and 5-years DFS, 3- and 5-years OS, successful organ preservation at 1 and 3 years, radiological response after induction chemotherapy, radiological response after chemoradiotherapy, toxicity of induction chemotherapy, toxicity of chemoradiotherapy, dose modifications and treatment delays during induction chemotherapy, dose reductions and treatment delays during chemoradiotherapy, completion rate of induction chemotherapy, completion rate of chemoradiotherapy, the number of patients undergoing surgery, surgical characteristics, pathological response, specimen quality, radicality, post-operative morbidity, quality of life, work-productivity, and cost-effectiveness and -utility.

All outcomes are also determined for the registration arm (observational cohort). These outcomes are intended solely to provide exploratory insights, as the study was not specifically powered to compare outcomes of this cohort.

### Data collection, management, and statistical analysis

#### Data collection and management

Central and local data management will be performed by Clinical Trial Centre Maastricht (CTCM). Data will be collected in an ISO 27001 certified study database (CASTOR) with an electronic case report form, according to the Good Clinical Practice guidelines and the Dutch legal requirements.

#### Statistical methods

All analyses will be performed according to the intention-to-treat principle. Relevant baseline characteristics, including age, sex, WHO performance status, and ASA score will be summarised using descriptive statistics. Additionally, details regarding the primary tumour are summarised using descriptive statistics, such as the type of neoadjuvant treatment, date and type of primary surgery, TNM-stage, tumour histology and surgical radicality. Categorical variables will be presented as frequencies and percentages. Continuous data will be summarised using descriptive statistics (mean, standard deviation, median, minimum, maximum, interquartile range). Statistical tests will be two-sided, with a *p*-value of < 0.05 considered statistically significant.

The proportion of patients achieving pCR and those who started a watch-and-wait approach with sustained cCR at 1 year will be reported as counts and percentages, stratified by treatment allocation. Mixed-effects (‘’multilevel’’) logistic regression will be used to compare arm A and arm B, with a random intercept at the centre level. Results will be expressed as odds ratios and 95% confidence intervals (CI).

Time-to-event endpoints (regrowth-free survival, LRFS, DFS, DMFS, and OS) will be visualised using the Kaplan–Meier method, with group comparisons performed using mixed-effects Cox proportional hazards regression. Results will be expressed as hazard ratio (HR) with 95% CI. Median survival times and 3- and 5-year survival probabilities, along with 95% CIs, will be reported, with survival rates provided if median times are not reached.

For datasets with ≥ 5% missing data, multiple imputation using fully conditional specification will be applied to complete the dataset. The number of imputations will be set to the percentage of incomplete records, and predictive mean matching will be used to draw imputations for continuous variables. Rubin’s rules will be applied to pool results across the imputed datasets for relevant analyses.

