#### Definition of high-risk LARC

To ensure that only patients who are proven to be at higher risk of treatment failure and poorer prognosis, and thus likely to benefit from TNT, are included in this study, high-risk criteria (MEND criteria, Fig. 1) have been identified and are applied for inclusion. High-risk LARC is defined by MRI-detectable tumour characteristics, including at least one of the following:The presence of a T4b tumour or evident tumour invasion of the MRF (distance to MRF 0 mm AND thickening of the MRF over a length of ≥ 5 mm);Grade IV extramural venous invasion (EMVI);Tumour deposits (TD);The presence ≥ 2 enlarged lateral lymph nodes (≥ 7 mm).

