#### Recruitment and randomisation

All eligible patients with high-risk LARC presenting in one of the participating centres will be identified by their physician and discussed for eligibility during an MDT meeting. Randomisation will be performed by a central automatic randomisation tool (CASTOR) using block randomisation, with an arm A:arm B ratio of 1:1. Stratification will be performed per centre. Each patient is assigned a sequential subject number. The allocation is not blinded to the patient, the investigators or the treating physicians. This study will also include an observational cohort (registration arm) consisting of patients who meet the inclusion criteria but are not willing to participate in the randomised study, and opt for neoadjuvant chemoradiotherapy, followed by surgery or a watch-and-wait approach.

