#### Sample size

The primary endpoint of this study is the complete response rate (pCR or cCR). Based on current literature, we expect a 32.5% complete response rate in the neoadjuvant triplet chemotherapy group, compared to 20% in the neoadjuvant doublet chemotherapy group. A 12.5% increase in response rate, with a 5% significance level and 80% power, requires a total sample size of 382 patients. Accounting for a 3% drop-out rate, the total required sample size is 394 patients, with 197 patients in each study arm.

The sample size calculation excludes the observational (registration) cohort, which will depend on patient enrolment during the trial's inclusion period. Data from this cohort will be used for exploratory purposes only.

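### The stated primary model contains only arm and centre, and its only interval is for an odds ratio; prespecifying the four MRI entry criteria and adding a risk difference with CI would be a near-free improvement

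*Protocol article*

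**What the plan says.** All references are to the protocol article.

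- **Statistical methods.** Complete response is reported by arm as counts and percentages. The model for the comparison is a mixed-effects logistic one, and it "will be used to compare arm A and arm B, with a random intercept at the centre level". No baseline covariate is named in the model, and the MRI criteria are not among the baseline characteristics given as examples. For the form of the result, the section states "Results will be expressed as odds ratios and 95% confidence intervals (CI".
- **Sample size.** "A 12.5% increase in response rate, with a 5% significance level and 80% power, requires a total sample size of 382 patients". The assumed rates are 32.5% (triplet) and 20% (doublet). A 3% drop-out allowance brings the total to 394.
- **Recruitment and randomisation.** "Stratification will be performed per centre"; no other stratification factor is given.
- **Definition of high-risk LARC.** "High-risk LARC is defined by MRI-detectable tumour characteristics, including at least one of the following": T4b or evident mesorectal fascia invasion, grade IV EMVI, tumour deposits, and two or more enlarged lateral nodes.
- **Background.** These features are tied to local recurrence, distant metastasis and survival. No figure links them to complete response.

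**The concern.** Two features of the stated analysis do not make full use of the design.

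1. **Scale.** The design effect is an absolute difference, but the only planned interval is on the odds-ratio scale. An odds ratio maps to a given number of points only at a given control rate. The Discussion says the clinical question is whether the benefit of the triplet is large enough to justify its extra toxicity. That weighing needs an absolute difference with its uncertainty.
2. **Covariates.** The four MRI criteria are assessed before randomisation and are not stratified on, so they can differ between arms by chance. If they predict complete response, leaving them out of a logistic model costs some efficiency. How much is at stake depends on how prognostic they are, and the article does not say.

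**Working it through.** **Step 1. Reproduce the sample size and confirm its scale.** Inputs (Sample size; Statistical methods for two-sided tests): p_A = 0.325, p_B = 0.20, alpha 0.05 two-sided, power 0.80.

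n per arm = (1.960 + 0.842)² × [0.325 × 0.675 + 0.20 × 0.80] / 0.125² = 190.6, so 191 per arm and 382 in total. Then 382 / 0.97 = 393.8, so 394. Both stated figures reproduce exactly from the risk-difference formula with unpooled variance (the pooled version gives 388). The design scale is therefore the absolute difference.

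**Step 2. What the planned effect looks like on each scale.**

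- Odds ratio = (0.325/0.675) / (0.20/0.80) = 1.93.
- Risk ratio = 0.325/0.20 = 1.63.

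Holding the odds ratio at 1.93 and varying the control rate p, the difference is o/(1 + o) − p, with o = 1.93 × p/(1 − p):

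| Control rate | Difference at OR 1.93 |
|---|---|
| 10% | 7.6 points |
| 15% | 10.4 points |
| 20% | 12.5 points |
| 25% | 14.1 points |
| 30% | 15.2 points |

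The control rate is not certain. The Background cites complete response figures after TNT of 21.8%, 25.0% and 28%. The odds ratio and its interval alone therefore do not show how the result stands against 12.5 points.

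**Step 3. What can be had from the planned percentages.** If the planned rates were observed with 191 per arm, the crude standard error would be √[(0.325 × 0.675 + 0.20 × 0.80)/191] = 0.0446. The hand-computed 95% interval would be 12.5 ± 1.96 × 4.46, about 3.8 to 21.2 points. A reader can do this, but it is not a planned analysis and does not come from the centre-adjusted model.

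**Step 4. Power with and without the MRI criteria.** This step is simulated and rests on assumptions: four independent binary criteria with prevalences 60/40/35/15%, the same odds ratio per criterion for complete response, marginal rates fixed at 20% and 32.5%, 394 patients, 4,000 trials per setting, and centre effects not simulated.

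The entry rule matters. Without it, 0.40 × 0.60 × 0.65 × 0.85 = 13.3% of simulated patients would have no criterion and could not be enrolled. Removing them cuts the variance of the number of criteria per patient from 0.83 to 0.57, which shrinks what adjustment can gain. With the rule applied:

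| OR per criterion (assumed) | Arm only | Arm + four criteria |
|---|---|---|
| 1.0 | about 80% | no gain |
| 0.70 | 80.6% | 81.3% |
| 0.50 | 81.2% | 83.1% |
| 0.37 | 81.0% | 83.8% |
| 0.25 | 81.1% | 85.2% |

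The Monte Carlo standard error of each power is about √(0.81 × 0.19/4000) = 0.6 points. A repeat run gave gains of about 0, under 1, 1.5 to 2, about 3, and 4 to 5 points in the same order. The 0.25 row is extreme: it implies a control-arm response falling from 34% with one criterion to 3% with three.

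**Step 5. Effect of adjustment on the odds ratio.** Adjusting for prognostic factors moves the conditional odds ratio away from the marginal one. In a parallel simulation (382 patients, prevalences 60/40/40/15%, no entry rule), the conditional odds ratio was 1.95 to 2.14 against 1.93 for per-criterion odds ratios of 0.70 to 0.35. The standardised risk difference stayed at 12.4 to 12.6 points. Adjustment is thus a further reason to report the marginal difference.

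**The case against.** **The analysis as stated is legitimate, and this stands.** It accounts for the only stratification factor. A comparison without covariates is valid after randomisation, and chance imbalance is already covered by the type I error rate. A reader might infer that the trial is underpowered or its test biased. Neither follows: the sizing reproduces, and power without covariates is about 80% as planned. Any gain is on top of the target.

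**The absolute difference is not hidden, and this stands too.** A reader might infer that nothing on the 12.5-point scale will be reported. The article commits to counts and percentages by arm, from which the crude difference follows. What is missing is narrower: an absolute difference with a planned interval, consistent with the primary model.

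**The prognostic premise is assumed.** The Background supports a link to recurrence, metastasis and survival only. A large power gain is tempting to claim, and simulating without the entry rule gives 88 to 89% at an odds ratio of 0.25. Such patients could not all be enrolled, so that figure should not be used.

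**Data capture is inferred.** Entry needs at least one criterion. The article does not say that all four are recorded separately for every patient, although MRI review by a specialised radiologist under an SOP makes it likely.

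**The full protocol or analysis plan may already cover this.** That is possible, and it is why the point is put as an improvement. The article does, however, itself state the model and the effect measure, so the comment on those two choices stands.

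**Conclusion.** The point holds as an improvement to the stated analysis, not as an error or a contradiction. The scale part is firm: the trial is sized on a difference in proportions, while the only interval named is for an odds ratio, and an odds ratio of 1.93 corresponds to anything from 7.6 to 15.2 points for control rates of 10% to 30%. The covariate part is sound in direction but conditional in size: about 0 to 5 points of power, and no more than about 2 points for per-criterion odds ratios of 0.50 or weaker. It rests on the assumed prevalences, independence of the criteria before the entry rule, equal effects, and no centre effects in the simulation.

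**What to change.** 1. Confirm that each of the four MEND criteria is captured as its own yes/no item in the eCRF, from the MRI before randomisation, for every randomised patient.
2. Prespecify these four baseline items as fixed effects in the primary mixed-effects logistic model, beside arm and the random centre intercept.
3. From that model, report the standardised (marginal) risk difference with 95% CI next to the odds ratio, and state how it is pooled if multiple imputation is used.
4. Keep the model with arm and centre only as a sensitivity analysis.
5. Fix this before any comparison of outcomes by arm.

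The cost is analysis wording and an eCRF check. No extra patients, visits or procedures are needed, and the sample size stays as it is. If the criteria turn out not to predict response, the simulated loss is negligible.

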#### Sample size

The primary endpoint of this study is the complete response rate (pCR or cCR). Based on current literature, we expect a 32.5% complete response rate in the neoadjuvant triplet chemotherapy group, compared to 20% in the neoadjuvant doublet chemotherapy group. A 12.5% increase in response rate, with a 5% significance level and 80% power, requires a total sample size of 382 patients. Accounting for a 3% drop-out rate, the total required sample size is 394 patients, with 197 patients in each study arm.

The sample size calculation excludes the observational (registration) cohort, which will depend on patient enrolment during the trial's inclusion period. Data from this cohort will be used for exploratory purposes only.

### Safety and monitoring

#### Safety

The investigator shall report all serious adverse events (SAEs) and suspected unexpected serious adverse reactions (SUSARs) to the sponsor within 24 h of becoming aware of the event. The sponsor is responsible for reporting SUSARs to the European Medicines Agency (EMA) via the Eudravigilance database. Fatal or life-threatening SUSARs must be reported within 7 days, with a follow-up report due within 8 days. Non-fatal or non-life-threatening SUSARs must be reported within 15 days.

#### Data monitoring committee

To ensure patient safety throughout the study, a Data Safety Monitoring Board (DSMB) has been appointed to decide on the continuation of the study following the interim analysis. An interim analysis will be performed by the central data manager and the study statistician after 100 patients have entered a watch-and-wait approach or have undergone surgery. Inclusion will not be stopped at time of the interim analysis. The number of patients that cannot complete the full course chemoradiotherapy and the number of patients with major postoperative morbidity (Clavien-Dindo ≥ 3) will be tabulated and discussed with the DSMB. Looking at these safety and logistic aspects will have no consequences on the total sample size or the actual alpha level at final analysis. After the interim analyses, the DSMB will recommend continuation or discontinuation of the study.

#### Trial monitoring

The study will be monitored by a qualified monitor from the CTCM based on a predetermined monitoring plan.

#### Confidentiality

Patient information collected during this study will be managed in accordance with the Dutch General Data Protection Regulation (AVG). Additionally, the use of study numbers will preserve patient confidentiality.

## Discussion

The neoadjuvant treatment of patients with LARC has increasingly shifted towards TNT in recent years, in some cases triple-based, due to its proven higher rates of pCR, lower risk of distant metastases, and a potential effect on OS compared to chemoradiotherapy [5, 6, 21, 22, 25]. Nevertheless, the TNT approach remains a topic of debate, as previous studies have involved highly heterogeneous patient populations, which may have hindered the therapeutic impact of TNT on long-term oncological outcomes. Moreover, these studies have placed limited emphasis on evaluating organ-preserving strategies. The hypothesis exists that triplet-based neoadjuvant therapy may offer greater potential for organ-sparing treatments and improved long-term oncological outcomes compared to less intensive neoadjuvant strategies, particularly when patients are selected more accurately based on high-risk tumour characteristics. Therefore, the primary objective of this multicentre, parallel-arm, phase III study is to compare outcomes following a triple-based TNT regimen, consisting of FOLFOXIRI and chemoradiotherapy, with a less intensive doublet-based TNT regimen, consisting of CAPOX or FOLFOX and chemoradiotherapy, in a selected, homogeneous group of patients with non-metastasised LARC who meet at least one of the high-risk criteria ("MEND criteria"), associated with poorer prognosis.

This study seeks to determine whether the effectiveness of triplet TNT can be enhanced through improved patient selection based on well-defined high-risk tumour characteristics. Additionally, a key question for clinical practice is whether the potential oncological benefit of triplet-based TNT is clinically relevant enough to warrant the associated higher toxicity rates, or whether a doublet-based TNT regimen could suffice, offering potential advantages in terms of reduced toxicity and broader applicability for patients in daily practice. Moreover, although TNT has already been implemented internationally as the standard of care for patients with LARC, evidence supporting its superiority over chemoradiotherapy remains variable. Some authors have expressed criticism of TNT, citing a lack of convincing evidence for a clear survival benefit and questioning whether the available data can be reliably generalised across different healthcare systems [37]. Therefore, this study also includes an observational cohort to gain further insight into patients with high-risk LARC who will not undergo TNT and are treated with neoadjuvant chemoradiotherapy. Although the study is not powered for this comparison, the findings may contribute to a better understanding of the added value of triplet TNT compared with chemoradiotherapy alone.

In the context of this trial protocol, it may be questioned whether chemotherapy should be administered as induction or consolidation therapy, in light of the favourable outcomes regarding complete response rates and organ preservation following consolidation therapy observed in the OPRA and CAO/ARO/AIO-12 trials [38, 39]. However, the median interval from completion of chemoradiotherapy to restaging was 8 weeks in the induction chemotherapy arm, compared to 28.5 weeks in the consolidation chemotherapy arm [40]. A large cohort study showed that delaying surgery beyond 8 weeks after chemoradiotherapy increases the likelihood of achieving a pCR, suggesting that the induction chemotherapy group in the OPRA-trial may not have reached the full therapeutic effect at restaging [41]. It is hypothesised that induction chemotherapy may enhance tumour vascularity, thereby improving the efficacy of chemoradiotherapy and addressing early micro metastases. While induction chemotherapy may increase toxicity and postoperative complications, several phase II studies have reported manageable side effects and high compliance rates for subsequent chemoradiotherapy [42–44]. Moreover, administering chemoradiotherapy after induction chemotherapy extends the interval to surgery (waiting period of 10–14 weeks after chemoradiotherapy), which may allow patients more time to recover and will potentially enhance the downstaging effects of the chemoradiotherapy. Lastly, an enhanced effect of intraoperative radiotherapy (IORT), considered an additional treatment option for patients with high-risk LARC in the Netherlands, has been observed with a shorter time interval between preoperative (chemo)radiotherapy and IORT, though no evidence exits on outcomes after TNT in combination with IORT [45]. Given the potential benefits, administering neoadjuvant chemotherapy prior to chemoradiotherapy may be particularly advantageous for patients with high-risk LARC.

In summary, this is the first study to specifically focus on a high-risk subgroup within the LARC population, characterised by a poorer prognosis. This is a selective group of patients that has not been specifically addressed in previous studies, which have generally focused on broader LARC cohorts. Despite mixed evidence regarding the long-term benefits of TNT on oncological outcomes, TNT has been globally implemented as standard care for LARC patients, partly due to its positive impact on complete response rates and the potential for organ-preserving treatments. Triplet TNT may lead to improved oncological outcomes, particularly in high-risk LARC populations, but current literature lacks direct comparisons between TNT regimens. Moreover, it remains uncertain whether the potential oncological benefit justifies the risk of heightened toxicity associated with triplet-based TNT. This randomised controlled trial compares triplet-based TNT (FOLFOXIRI) with doublet-based TNT (CAPOX/FOLFOX) in a high-risk LARC population. The primary outcome, complete response rate, is of significant clinical relevance, particularly as it relates to organ-preserving strategies.Secondary outcomes will assess long-term oncological results. The results of this study are expected to contribute to more tailored treatment strategies, potentially enhancing both oncological outcomes and quality of life.

